### Sample Size

Prior to launching a definitive randomized controlled trial, it is essential that the feasibility of conducting such a trial be demonstrated. A sample for a definitive study with multiple end-points and outcome variables will require several hundred participants and warrant a multi-site study. Given that no study has examined the effect of exercise on cognitive function in SIVCI, we have selected a sample size of 30 participants per group. Studies have suggested a standard deviation of change of 6 to 7 [27-29] in Alzheimer Disease Assessment Scale Cognitive (ADAS-Cog) scores among individuals with vascular cognitive impairment. We highlight that a recent exercise trial among seniors at risk for AD with ADAS-Cog as the primary outcome measure demonstrated an effect size of 0.60 [30]. Thus, assuming an alpha of 0.05, 30 participants per group will provide a power of 0.75 to 0.80. We estimate a drop-out rate of 10% during a 12-month period. Hence, we are aiming to recruit 35 participants per group (i.e., 70 participants in total) which will accommodate a conservative 15% drop-out rate.

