### Statistical Analyses

As a primary objective of this study is to provide preliminary evidence of **efficacy **we will compare participants of the AT group who are compliant with the intervention (defined as attending 60% of the total exercise sessions) to the CON group rather than using an intention-to-treat analysis as would be appropriate in a pivotal clinical trial. In addition, no adjustment for multiple endpoints will be made since in a proof-of-concept study a Type II error is of more concern than a Type I error [52]. For each of the three primary endpoints (i.e., ADAS-Cog, EXIT-25, ADCS-ADL), the change from baseline to six months and 12 months will be assessed using an analysis of covariance model incorporating the baseline measurement. Observing a statistically significant difference on **any **of the three primary outcomes will be considered preliminary evidence of efficacy.

We will also report variances, co-variances, and effect sizes, as well as sampling feasibility (i.e., ease of recruitment, recruitment rate, withdrawal rate). This information will inform sampling for future trials.

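### The 35-per-group target allows for drop-out only; the efficacy comparison also excludes AT participants below 60% attendance, and neither the 30 per group nor its stated power provides for that loss

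*Protocol article*

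**What the plan says.** All places are in the protocol article, under Methods/Design.

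- **Sample Size, basis of power.** "Thus, assuming an alpha of 0.05, 30 participants per group will provide a power of 0.75 to 0.80". The effect size comes from a cited exercise trial that "demonstrated an effect size of 0.60".
- **Sample Size, drop-out.** "We estimate a drop-out rate of 10% during a 12-month period". To leave a margin over this, the plan is to "recruit 35 participants per group (i.e., 70 participants in total) which will accommodate a conservative 15% drop-out rate". No other loss is named.
- **Randomization.** Allocation is 1:1, so the AT arm is not enlarged.
- **Statistical Analyses.** The efficacy comparison is not by intention to treat. Its AT side is limited to "participants of the AT group who are compliant with the intervention (defined as attending 60% of the total exercise sessions", and this set is compared with the CON group. The rule has no counterpart on the CON side.

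The article gives no expected rate of compliance with the 60% rule.

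**The concern.** The sample size and the analysis set are defined in two sections that do not refer to each other. One counts everyone who stays in the trial. The other counts, on the AT side, only those who stay and also attend enough classes. The step from 30 to 35 covers the first condition alone.

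What is at stake is the number analysed in AT and the power claimed for it. The Statistical Analyses section says that a Type II error is of more concern here than a Type I error, so an unbudgeted loss of power is the risk that the authors themselves rank first. The trial is also meant to inform the size of a definitive trial, and a sample size statement that leaves out one of two sources of loss is a poor model for that.

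**Working it through.** **Inputs.** From Sample Size: 30 per group for power; effect size 0.60; alpha 0.05, with sidedness not stated; drop-out 10% expected and 15% allowed; 35 recruited per group. From Statistical Analyses: AT participants below 60% attendance are left out of the comparison. The compliance rate is not in the article, so 90%, 80% and 70% of AT completers are assumed values.

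**Formula.** Power is from the noncentral t distribution with n1 + n2 - 2 degrees of freedom and noncentrality 0.60 / sqrt(1/n1 + 1/n2).

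**1. The stated power.** For 30 against 30, noncentrality = 0.60 / sqrt(1/30 + 1/30) = 2.32. Power is 0.74 one-sided and 0.63 two-sided (normal approximation: 0.751 and 0.642). The lower end of the stated range is therefore reproduced with a one-sided alpha of 0.05. Two-sided, effect size 0.60 alone does not reach it.

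**2. The stated recruitment.** 30 / (1 - 0.15) = 35.3, and 35 x 0.85 = 29.75. The article's 35 is, to rounding, the number that leaves 30 per arm after 15% drop-out.

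**3. Room left for low attendance in AT.**
- At 15% drop-out, 29.75 completers remain. The margin is used up, and any completer below 60% attendance puts AT under 30.
- At 10% drop-out, 35 x 0.90 = 31.5 remain. AT stays at 30 only if at most 1 - 30/31.5 = 4.8% of completers fall short, which is about one person.

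**4. Power once AT is reduced.** CON is held at 30 and AT is 30 x compliance.

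| Assumed compliance among AT completers | AT vs CON | Two-sided | One-sided |
|---|---|---|---|
| 100% | 30 vs 30 | 0.63 | 0.74 |
| 90% | 27 vs 30 | 0.60 | 0.72 |
| 80% | 24 vs 30 | 0.58 | 0.70 |
| 70% | 21 vs 30 | 0.54 | 0.67 |

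The loss is about 2 points at 90% compliance, about 5 at 80% and about 8 at 70%, and nearly the same on either reading of alpha. It stays moderate because CON is not reduced.

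**The case against.** **Might AT still reach 30?** Yes. A reader might infer that AT is bound to fall below 30. The article does not support that, because it gives no compliance rate. The expected drop-out of 10% covers 12 months, so fewer may be lost by the six-month assessment. Someone who stops attending and then withdraws is lost once, not twice. Eligibility also asks for ability to comply with visits and treatment plan. All of this limits the size of the shortfall. It does not supply an allowance for participants who return for assessment but attended too few classes, and the 60% rule has a purpose only if some such participants are expected.

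**Is the word conservative wrong?** No. It describes 15% allowed against 10% expected, which is true. The article does not claim that it covers the complier comparison. The step from 30 to 35 is also sound for drop-out alone.

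**Is the stated power itself an error?** That is a separate question. One-sided, 0.75 is reproduced; the two-sided 0.63 is not proof of a mistake, because sidedness is not stated and the planned covariance adjustment for baseline could add power (a correlation of 0.5 would bring the two-sided figure to 0.75). The point here is the drop from whichever starting value applies.

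**Would analysing everyone as assigned solve it?** Not for power. Suppose, for illustration, that 0.60 is the effect in compliers and non-compliers gain nothing. At 80% compliance the all-randomised effect is 0.80 x 0.60 = 0.48, and two-sided power with 30 per arm is 0.45, against 0.58 for 24 compliers. Whether 0.60 is an effect in compliers or in all randomised cannot be told from the article. Replacing the declared comparison would also change the question asked, so it is more than a change of wording. This part of the objection stands.

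**Is it too small to matter in a proof-of-concept trial?** A few AT participants fewer would not defeat the feasibility aims. The correction is still worth making, because it costs little and concerns a figure on which the plan relies.

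**Conclusion.** The point holds in this form: the planned comparison removes low attenders from AT, and the sample size makes no provision for it. The stated 30 per group and its power describe all completers, not the set to be compared. At the 15% drop-out allowed there is no room for any non-compliant completer; at 10% there is room for about one.

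The size depends on a compliance rate that the article does not give. The power figures also assume effect size 0.60, no gain from covariance adjustment, and low attendance counted on top of drop-out. Overlap between the two would make the loss smaller. On these assumptions, power at 90% compliance or less is below the stated range on either reading of alpha. This should be corrected, but it does not put the trial in doubt.

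**What to change.** In Sample Size, replace the single statement of 30 per group with power 0.75 to 0.80 by three items for the complier comparison:

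1. the assumed compliance rate among AT completers;
2. the resulting AT and CON numbers, for example 24 against 30 at 80%;
3. the matching power, with the sidedness of alpha named (in that example 0.58 two-sided or 0.70 one-sided).

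In Statistical Analyses, keep the declared comparison and add an analysis of all randomised participants with follow-up data, as assigned. The figure of 35 x 0.85, about 30 per arm, does apply to that analysis.

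The cost is a less favourable stated power and one additional analysis. No extra patients are needed. Keeping 30 evaluable compliers in AT instead would take more recruits: at 80% compliance, 30 / (0.85 x 0.80) = 44.1, so 45 in that arm.

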### Measurements

Baseline measurements will be obtained prior to randomization. There will be three measurement sessions: baseline, 6 months, and 12 months (Figure 1). Outcomes will be assessed by trained assessors blinded to group allocation.

#### Screening Session

For the screening session, we will administer the Physical Activity Readiness Questionnaire (PAR-Q) [31], a screening measure of physical readiness for exercise. Global cognitive function will be assessed using the MMSE [26] and the MoCA [25].

#### Descriptors

Using a wall mounted stadiometer, standing height will be measured as stretch stature to the 0.1 cm per standard protocol. Weight will be measured twice to the 0.1 kg on a calibrated digital scale. General health and socioeconomic status will be ascertained by a questionnaire. Participants will undergo a clinical assessment with neurologist and study physicians ([name] and PL) at baseline to confirm current health status and eligibility for study, including clinical impressions of overall cognitive and functional status. The Neuropsychiatric Inventory (NPI), an informant-rated instrument, will be used to evaluate behavioural and neuropsychiatric symptoms [32].

Physical activity, not including the study-assigned exercise classes, will be determined by the valid and reliable Physical Activities Scale for the Elderly (PASE) questionnaire [33,34]. Designed for those aged 65 years and older, participants use a 12-item scale to self-report the average number of hours per day spent participating in leisure, household, and occupational physical activities over the previous seven-day period. Accounting for extracurricular physical activities throughout the randomized trial is essential to ascertain the specific effects of the delivered interventions on cognition and function.

#### Primary Outcomes

##### Cognitive Function 

We will assess cognitive function using the cognitive section of the Alzheimer Disease Assessment Scale (ADAS-Cog) [35]. The scale consists of 11 brief cognitive tests assessing memory, language, and praxis. Scores range from 0 to 70, with higher scores indicating greater severity of cognitive impairment. The ADAS-Cog has been a significant outcome measure in numerous trials with AD [27,36,37] but also with vascular dementia [29,38]. The ADAS-Cog has marked advantages as an outcome measure, based on its substantial data confirming both reliability and validity and its use in measuring longitudinal change together with sensitivity to treatment effects [39].

##### Global Executive Function 

Because executive dysfunction is common among those with SIVCI [6], we will use the Executive Interview (EXIT-25) [40] to assess global executive function. The EXIT 25 provides a standardized clinical assessment of executive functions. It contains 25 items designed to elicit signs of frontal system pathology. Performance on the EXIT25 correlates well with standard neuropsychological tests of executive functions. The EXIT25 scores range from 0 to 50, with high scores indicating impaired global executive function. A cut point of 15 out of 50 is recommended [40].

##### Everyday Function

Because executive dysfunction is associated with impaired everyday function [7], we will use the ADCS-ADL to assess the ability to perform everyday activities of daily living [41]. The ADCS-ADL is a 23-item informant-rated questionnaire that measures, in a range of 0 to 78, an individual's performance of activities of daily living.

#### Secondary Outcomes

##### Blood Biomarkers 

Serum glucose, Hgb A1c, and lipid level will be measured by conventional methods. Serum HSC, CRP, and IL-6 will be determined by standard ELISA methods [42].

##### Physical Function 

Physical function will be assessed using a three-instrument performance battery that includes:

1) Six-Minute Walk 

This is a walking test of physical status to assess general cardiovascular capacity in seniors [43]. The total distance walked in meters in six minutes is recorded in meters.

2) Balance and Mobility 

General balance and mobility will be assessed with the National Institute on Aging (NIA) Balance Scale [44]. For this Scale, participants are assessed on performances of standing balance, walking, and sit-to-stand. Each component is rated out of four points, for a maximum of 12 points. Poor performance on this scale predicts subsequent disability [44].

3) Physiological Falls Risk 

We will use the Physiological Profile Assessment (PPA)^© ^[45] (Prince of Wales Medical Research Institute, Randwick, Sydney, NSW, Australia) to assess for physiological falls risk. The PPA is a valid and reliable tool for assessing fall risk in older people. Based on the performance of five physiological domains (postural sway, hand reaction time, quadriceps strength, proprioception, and edge contrast sensitivity), the PPA computes a fall risk score for each individual and this measure has a 75% predictive accuracy for falls in older people [45]. A PPA z-score of 0-1 indicates mild risk, 1-2 indicates moderate risk, 2-3 indicates high risk, and 3 and above indicates marked risk [46].

4) Quality of Life 

We will evaluate health related quality of life using the EuroQol 5D (EQ-5D) -- a preference-based generic utility instrument that provides weightings for quality adjusted life year (QALYs). QALYs are defined as the benefit of a health intervention in terms of time in a series of quality-weighted health states, in which the quality weights reflect the desirability of living in the state, typically from "perfect" health (weighted 1.0) to dead (weighted 0.0) [47]. QALYs are calculated based on the quality of life of a patient (measured using health utilities) in a given health state and the time spent in that health state. The EQ-5D captures 243 unique health states based on the following domains: 1) mobility; 2) self-care; 3) usual activities; 4) pain and 5) anxiety or depression. We will calculate QALYs using the health state utility values from the EQ-5D to determine if there is a statistically significant difference in the incremental cost per QALY change for participants receiving the aerobic-based training compared with those who are not.

5) Health Resource Utilization 

The health resource utilization questionnaire asks participants to report the following visits over a specified time period: 1) health care professionals; 2) admissions or visits to hospital; and 3) laboratory work. The health resource utilization questionnaire has been previously described and supported in previous studies [48]. We will estimate total health care related costs over the 12 months from a Canadian health care system perspective. Participants will be instructed to specify total health care expenditure and report the reason for each item. Additionally, participants will be instructed to report health care expenditure due to any adverse events associated with the aerobic-based training program; this is not anticipated to be a major cost driver. On a per participant basis, costs will be assigned to health care resource utilization using a fully allocated hospital cost model (for in-patient costs) and the British Columbia provincial guide to medical fees (for outpatient costs). Our base case analysis will consider the costs of all health care resource use and our sensitivity analyses will include only intervention related health care resource costs and a complete case analysis.

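### The separate adverse-event cost item is tied to the exercise programme and self-attributed, so only the exercise arm can answer it and an answer could disclose allocation to whoever handles the form

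*Protocol article*

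**What the plan says.** Health resource utilization is listed among the Secondary Outcomes of the protocol article and is collected by a questionnaire that participants answer. Four statements under that heading matter here.

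- A general item, not restricted by arm: "Participants will be instructed to specify total health care expenditure and report the reason for each item".
- A further item on top of it: "Additionally, participants will be instructed to report health care expenditure", which the same sentence limits to adverse events arising from training. The full restriction is that "participants will be instructed to report health care expenditure due to any adverse events associated with the aerobic-based training program". The authors add that "this is not anticipated to be a major cost driver".
- The main cost analysis: "Our base case analysis will consider the costs of all health care resource use".
- The supplementary ones: "our sensitivity analyses will include only intervention related health care resource costs and a complete case analysis".

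Elsewhere, the Measurements section states without exception: "Outcomes will be assessed by trained assessors blinded to group allocation". Allocation Concealment extends blinding to data analysis and says that participants cannot be blinded. Adverse Events Monitoring has all reported events reviewed monthly by a group that includes a physician and a statistician from outside the research team. It does not connect that review to the cost data.

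**The concern.** The extra item is worded around an exposure that only one arm has. Three consequences follow.

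1. **Unequal prompting.** AT participants get a second chance to recall health care spending and control (CON) participants do not. The population is selected for impaired recall, so a second prompt could plausibly recover costs that the general item missed.
2. **Attribution.** The respondent must decide that an event was caused by exercise. That respondent knows the allocation and has cognitive impairment, and no informant or clinician check is described for this item.
3. **Blinding.** Any positive answer identifies the participant as AT. If the form passes through the hands of someone who also rates the ADAS-Cog or EXIT-25, the single-blind design is weakened for that participant.

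At stake are the even-handedness of cost collection, the meaning of the sensitivity analysis limited to intervention-related costs, and a possible route to unblinding.

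**Working it through.** No alpha, rate, standard deviation or sample size enters this point, and the article gives no figure to reproduce. The check sets the statements against each other.

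**Step 1: who can answer each item?** The general item asks every participant for total spending and the reason for each entry. A fall or an admission in CON is therefore recorded, with its cost and reason. The added item needs an event linked to the training programme. The section on the Usual Care group gives CON educational material only, so no CON participant can have a qualifying event. The one-sidedness belongs to the added item, not to adverse-event costs as a whole.

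**Step 2: does it affect the base case?** The base case uses all resource use, which the general item captures in both arms. There are two possibilities.

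- If the added item only labels spending already reported under the general item, total cost is unchanged.
- If it brings in spending that the general item missed, mean AT cost rises by some amount *c* with no counterpart in CON. The Economic Analysis section defines ICER = ΔCost/ΔEffect, so it becomes (ΔCost + *c*)/ΔEffect, a shift of *c*/ΔEffect. For a positive ΔEffect this counts against the intervention.

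The article gives no value for *c* and expects this cost category to be small.

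**Step 3: does it affect the sensitivity analysis?** The article does not say how a cost is classed as intervention-related. The added item is the only collection step explicitly tied to the intervention, so it is a natural candidate. The recorded reason for each entry could also serve. If the added item is used, the classification rests on unverified lay attribution. Eligibility requires a memory deficit and a MoCA below 26, and admits MMSE scores as low as 20. For other measures in the same population, the NPI and the ADCS-ADL, the article relies on an informant. No such check is stated here.

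**Step 4: who sees the answer?** Health resource utilization is an outcome, and Measurements assigns outcomes to blinded assessors. Taken literally, that puts this questionnaire with blinded staff. But the Health Resource Utilization text says only that "The health resource utilization questionnaire asks participants to report the following visits over a specified time period". It names nobody who administers or reads the form and does not place it before or after cognitive testing. Disclosure to a rater is therefore possible on the stated arrangement but not established.

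**The case against.** The strongest reply is that the item is only a supplement. Both arms report all spending with reasons, the base case uses all of it, and safety events are reviewed monthly whatever the arm. Costs caused by training are zero in CON by definition, so a zero there is no error. The classification of costs and the handling of forms are details that an article commonly leaves to the full protocol or analysis plan. The outcome is exploratory, and the authors expect the item to contribute little.

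Most of this stands, and it rules out three stronger readings that a reader might infer.

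- **That adverse-event costs can be reported only by AT.** The sentence immediately before the added item contradicts this.
- **That the AT versus CON cost comparison cannot be interpreted.** The planned main comparison is of all costs and does not depend on the added item, apart from the possible extra recall in Step 2.
- **That the ADAS-Cog and EXIT-25 raters will be unblinded, in some countable number of participants.** No handler is named and no reporting rate is given, so any count would be invention.

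The objection does not dispose of the item itself. Its wording is stated in the article, not left out of it. That wording creates a prompt in one arm only, asks an unblinded respondent to judge cause, and invites an answer that names the allocation. The general item already asks for reasons, so the training-specific wording gains little that could not be obtained neutrally.

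**Conclusion.** The point holds for the dedicated item and no further. As worded, the item can be answered only in AT and depends on self-attribution by unblinded participants with cognitive impairment. It also discloses allocation to anyone who reads a positive answer. The base-case cost comparison stands, subject to a possible small upward shift in AT cost.

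This is a minor point on an exploratory secondary outcome in a proof-of-concept trial. Its size cannot be computed from the article. It rests on three conditions that the article leaves open: that the extra prompt recovers costs not otherwise reported, that the item feeds the intervention-related sensitivity analysis, and that someone who rates outcomes handles the form. The one-sided wording needs none of these conditions, and correcting it costs very little, so the change is worth making.

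**What to change.** 1. Replace the added item with one neutral question, worded identically for both arms: spending due to any adverse event or new health problem since the last assessment, with the reason.
2. Have the existing adverse-event reviewers assign relatedness to training afterwards, and define intervention-related costs for the sensitivity analysis from that judgement.
3. Give the questionnaire after the cognitive tests, or as a self-completed form that the raters do not see. The second option protects better. A form read after testing at 6 months could still inform the same rater at 12 months, and a free-text reason can disclose allocation even under neutral wording.

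The cost is one reworded item, slightly longer answers from CON, and a small added task for reviewers who already meet monthly. No extra visit, participant or outcome measure is needed.
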